## Ethical considerations

The original version of this trial protocol has been approved by the Ethics Committee of the Karolinska Institutet, Stockholm (Dnr 2022-02084-01).

Physical exercise during chemotherapy is deemed feasible and safe^19^. Potential adverse events, such as cardiovascular and musculoskeletal symptoms, will be recorded throughout the NACT period and participants who experience serious adverse events will discontinue trial participation. Adverse events that are ascribed NACT but not the trial intervention will be handled in accordance to clinical routine by the responsible oncologists. There is no evidence that the intervention may lead to inferior results concerning the primary or secondary endpoints. Instead, there are data from studies in the adjuvant setting showing a preserved health-related quality of life, lower rate of self-reported symptoms related to treatment, and higher chemotherapy completion rates. In addition, this trial offers patient empowerment that is generally experienced as a positive aspect of treatment. Therefore, participation in this trial is judged ethically highly feasible.

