## Population

Clinically T1-3, N0-2 BC patients scheduled for NACT and surgery with curative intent and fulfilling all inclusion criteria and no exclusion criteria as listed below. Patients with oligometastases scheduled for such curative treatment are eligible. Baseline stratification is performed based on treating hospital and biological tumour subtype (ER+HER2-, ER+HER2+, ER-HER2+, ER-HER2-) prior to randomization.

Eligible patients are identified at pre-NACT multidisciplinary team conferences and then receive information about the trial by their oncologist or surgeon, avoiding undue delays. Informed consent is mandatory before randomization and can be obtained by physician or nurse with the appropriate delegation. All participants will undergo standardised tests of physical condition and strength before start of NACT and after NACT but before surgery.

| **Inclusion criteria** | **Exclusion criteria** |
| --- | --- |
| - Patients with primary invasive breast cancer cT1-T3 cN0-2 - Full tumour biology available before initiation of NACT (ER, PR, HER2, tumour grade, and Ki67) - Written informed consent - Age ≥ 18 years | - Bilateral invasive breast cancer - Pregnancy or breast-feeding - The presence of musculoskeletal, neurological, respiratory, metabolic or cardiovascular conditions that may prevent safe completion of the exercise and testing demands of the study - Currently performing equal to or more than 150 mins of moderate to high intensity aerobic exercise and 2 sessions per week of moderate intensity resistance exercise (WHO criteria) |

In case of pre-term abortion of NACT, participants may remain on the trial. Participants who have not received at least four treatment cycles (three weekly treatments of e.g. paclitaxel correspond to one treatment cycle) as NACT are excluded from per-protocol analyses (see statistical analysis plan).

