## End of trial

The trial will end for each participant followed for two years after the date of surgery, but also for participants who die, withdraw consent or are lost to follow-up.

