| Not related | The AE is clearly not related to the trial intervention. It is independent of trial intervention, or evidence prevails that it is related to other aetiology. |
| --- | --- |
| Unlikely | The AE is doubtfully related to the trial intervention. Temporal association between the AE and the trial intervention and the nature of the AE is such that the trial intervention is not likely to have had any reasonable association with the observed AE (cause and effect relationship improbable but not impossible). |
| Possibly | The AE may be related to the trial intervention. Less clear temporal association; other aetiologies also possible. |
| Probably | The AE is likely related to the trial intervention. Clear-cut temporal association; a potential alternative aetiology is not apparent. |
| Definitely | The ae is clearly related to the trial intervention. Clear-cut temporal association, and no other possible cause. |

Severity assessment: Local investigators make a severity assessment of the event according to the Common Terminology Criteria for Adverse Events Version 5 published November 27, 2017^34^.

| Grade 1 | Mild; asymptomatic or mild symptoms; clinical or diagnostic observations only;  intervention not indicated. |
| --- | --- |
| Grade 2 | Moderate; minimal, local or non-invasive intervention indicated; limiting age-appropriate instrumental ADL. |
| Grade 3 | Severe or medically significant but not immediately life-threatening;  hospitalization or prolongation of hospitalization indicated; disabling; limiting  self-care ADL. |
| Grade 4 | Life-threatening consequences; urgent intervention indicated. |
| Grade 5 | Death related to AE. |

A Semi-colon indicates ‘or’ within the description of the grade. ADL: activities of daily living

AEs have to be reported as SAE only when they are related (possibly, probably, definitely) to trial intervention. AEs related to NACT or adjuvant therapy are not considered as a SAE and are therefore exempted from expedited reporting. Trial intervention-related SAEs are documented and reported immediately (within a maximum of 24 hours) to the Principal Investigators.

All AEs will be followed until they have abated, or until a stable situation has been reached. Depending on the event, follow-up may require additional tests or medical procedures as indicated, and/or referral to a general physician or a medical specialist.

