## Estimated sample size and power

Patients will be randomized in a 1:1 fashion. It is anticipated that the rate of the primary endpoint pCR will be approximately 30% in the control arm. We aim to increase the rate of pCR in the experimental arm to 40%, i.e. a 10 percentage points increase, which is regarded clinically relevant since it would translate into improved disease-related outcomes. With a power of 80% and an alpha of 5%, a total of 712 patients have to be included; 356 in each arm. Accounting for a drop-out of 10%, we aim to include 790 patients. Stratification at the moment of computerized randomization will be done based on site of treatment (hospital) and biological tumour subtype (ER+HER2-, ER+HER2+, ER-HER2+, ER-HER2-).

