## Statistical analysis plan

All outcomes will primarily be analysed using an intention-to-treat approach, i.e. all study subjects will belong to the treatment group (exercise intervention or control) they were assigned to, disregarding compliance. As sensitivity analysis, all outcomes will also be analysed using a per-protocol approach, meaning that participants in the intervention group who comply with less than 65% of the prescribed physical exercise program or complete less than 40% of the planned neo-adjuvant systemic therapy (around two 3-weekly courses) will be excluded from analysis.

*Covariate adjustment in statistical models*

Guidelines from the European Medicines Agency (EMA) regarding statistics and covariate adjustments recommend that factors that are used to stratify the randomization, i.e. site of treatment and biological tumour type in this trial, should be accounted for in the statistical analysis^35,36^. However, it is also recognized that “limited numbers of subjects per centre will make it impracticable to include the centre effects in the statistical model”. In this trial it is very likely that some of the centres will contribute few patients, which may cause problems in some of the statistical models, in particular for the categorical outcomes (such as the primary endpoint, pCR) where the variability in the outcome may be too small within each site. Hence, the statistical models, described below, will primarily be adjusted for biological tumour type and not for study site. If appropriate and if the data allows (i.e. no convergence problems and not too small subgroups), the site effect will also be incorporated in the models as a random effect in the mixed models and as a fixed factor in the remaining logistic regression models.

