#### Handling missing values and deaths

Experience from previous studies have shown that this group of patients are in general highly motivated to fully participate in trials, including answering questionnaires, undergo physical exams and other assessments. Hence, it is anticipated that the dropout rate and the number of missing values will be low in both treatment arms and that this will be a minor problem in this study. Furthermore, the number of deaths during this relatively short follow-up period is also expected to be low. Nevertheless, sensitivity analysis will be performed where missing values will be assumed to be missing at random, MAR. This assumption will be already accommodated in the mixed models where repeated measurement outcomes will be analysed. For the remaining outcomes multiple imputations, assuming MAR will be performed.

A data monitoring committee consisting of three independent experts will perform a safety analysis with the purpose to assess the recruitment to the trial and the rate of adverse events, and to make sure that patients in the intervention group do not appear to fare significantly worse than patients in the standard of care group. The committee may recommend terminating the study if a significant benefit in favour of one group is shown, such that the HR for intervention versus standard of care significantly (p=0.001) exceeds 1, if the recruitment is so low that that the necessary number of events is unlikely to be reached or if there are serious concerns about unexpected AEs in the intervention group. If the committee determines that it is safe to proceed with the study, the results of the analysis will remain unknown to everyone except the committee members.

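### The Protocol takes participants with a serious adverse event out of the trial, against its own intention-to-treat and end-of-trial rules, so pCR can go missing almost only in the exercise arm

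*Protocol*

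**What the plan says.** All references are to the Protocol.

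- **Ethical considerations:** "participants who experience serious adverse events will discontinue trial participation". The sentence speaks of the trial, not of the exercise programme, and says nothing about outcome data afterwards.
- **End of trial:** participation ends two years after surgery, and "also for participants who die, withdraw consent or are lost to follow-up". An SAE is not on the list.
- **Statistical analysis plan:** under the primary approach, "all study subjects will belong to the treatment group (exercise intervention or control) they were assigned to, disregarding compliance".
- **Adverse Events:** "AEs have to be reported as SAE only when they are related (possibly, probably, definitely) to trial intervention". The section also says that events due to NACT or adjuvant therapy are not to be documented as SAEs.
- **Withdrawal:** data already entered in the eCRF are kept unless the participant objects. Data arising later are not mentioned.
- **Outcomes, Variables and measures:** pCR is read from the surgical specimen, about five months after NACT starts, with central review of the slides.
- **Population:** "In case of pre-term abortion of NACT, participants may remain on the trial".
- **Handling missing values and deaths:** few missing values are expected. A sensitivity analysis under MAR is planned; repeated-measures models are said to accommodate it, and "For the remaining outcomes multiple imputations, assuming MAR will be performed". pCR is one of those remaining outcomes.

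**The concern.** A site that follows the Ethical considerations literally stops collecting data on a randomised patient whom the intention-to-treat rule requires in the analysis. The reporting rule makes this one-sided. Controls do not receive the trial exercises, so an event judged related to the intervention will be rare or absent among them.

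What is lost is the primary endpoint. An SAE during NACT comes before surgery, so no pCR result yet exists for the Withdrawal section to preserve. Surgery and pathology will normally still take place as routine care, but no section says that the result and the slides are still retrieved. A separate statistical analysis plan could choose a missing-data method, but it could not recover results that sites had been told not to collect.

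If those who leave reach pCR less often than the rest of their arm, the exercise arm looks better than it is. The MAR sensitivity analysis would give much the same answer as leaving them out.

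**Working it through.** **1. Sections side by side.** The end-of-trial list and the intention-to-treat rule both keep a patient with an SAE in the trial. The Ethical considerations take the patient out. The three can agree only if discontinuing there means leaving the exercise, and the text does not say that.

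**2. The plan's own figure.** Inputs from Estimated sample size and power: "the rate of the primary endpoint pCR will be approximately 30% in the control arm", and the aim is to "increase the rate of pCR in the experimental arm to 40%, i.e. a 10 percentage points increase"; 80% power, 5% alpha, 1:1 allocation. The primary endpoint section makes the test two-sided. With pooled variance and no continuity correction:

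n per arm = [1.960·√(2·0.35·0.65) + 0.842·√(0.30·0.70 + 0.40·0.60)]² / 0.10² = 356, or 712 in total.

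This matches. The drop-out step gives 712/0.90 = 791, against the stated 790, a trivial rounding difference. Power is 80.0% with 356 evaluable per arm and 83.9% with all 395 per arm.

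**3. Size of the possible bias.** The Protocol gives neither an SAE rate nor the pCR rate among such patients, so both are assumptions:

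- f = share of the exercise arm that exits before surgery, 1% to 10%; control 0%.
- q = true pCR rate among those who exit, from 40% (like their arm) down to 0%.
- p = true pCR rate in the whole exercise arm, 40%; control 30%.

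Under a complete-case analysis, or MAR imputation from arm and tumour subtype alone, the expected exercise-arm rate is (p − f·q)/(1 − f). The overstatement is that value minus p. For f = 5% and q = 0: 0.40/0.95 = 0.4211, so 2.11 points.

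| Exits f | q = 40% | q = 20% | q = 0% |
|---|---|---|---|
| 1% | 0.00 | 0.20 | 0.40 |
| 2% | 0.00 | 0.41 | 0.82 |
| 5% | 0.00 | 1.05 | 2.11 |
| 10% | 0.00 | 2.22 | 4.44 |

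(Overstatement of the 10-point difference, in percentage points.)

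**4. No true effect.** With p = 30% in both arms, the spurious difference is d = (0.30 − f·q)/(1 − f) − 0.30. The two-sided rejection rate is Φ[(d − 1.96·SE₀)/SE₁] + Φ[(−d − 1.96·SE₀)/SE₁], with 395 controls and 395·(1 − f) exercise patients; SE₀ is pooled and SE₁ unpooled.

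| Exits f | Spurious difference, points (q = 30% to 0%) | Rejection rate |
|---|---|---|
| 1% | 0 to 0.30 | 5.0–5.1% |
| 2% | 0 to 0.61 | 5.0–5.4% |
| 5% | 0 to 1.58 | 5.0–7.6% |
| 10% | 0 to 3.33 | 5.0–16.6% |

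**The case against.** The best defence is that the sentence in the Ethical considerations is loose wording for leaving the exercise programme. Surgery and pathology are standard care, intention-to-treat is stated, and missingness is expected to be low. On that reading nothing is lost. This is plausible, and it is why the point says that pCR *can* be lost, not that it will be. It does not remove the conflict: the sentence names the trial, and a site has no other text telling it to keep collecting.

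A second objection also stands in part. The Adverse Events section defines an SAE by seriousness alone and brings in relatedness only for reporting. That exits fall almost only in the exercise arm is therefore an inference from the reporting rule, though a reasonable one.

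A reader might infer more than the Protocol supports:

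- *That the primary analysis imputes pCR under MAR.* MAR is introduced as a sensitivity analysis. No primary rule for a missing pCR is fixed, and a separate analysis plan may supply one.
- *That those lost are the patients who do worst.* The potential adverse events named in the Ethical considerations are cardiovascular and musculoskeletal, and NACT-related events are outside the rule. Nothing links an exercise-related SAE to lower pCR.
- *That patients who end NACT early drop out of the primary analysis.* The Population section excludes those with too few cycles only from per-protocol analyses, which suggests that they stay in intention-to-treat.
- *That the trial's result is shifted by a definite amount.* Suppose losses of 5% in control and 10% in exercise, none with pCR. Then 30% v 40% among the operated becomes 0.95 × 30% = 28.5% v 0.90 × 40% = 36.0%, and a true 30% in both arms appears as 31.6% v 33.3%. The arithmetic is right, but the split has no source, and zero pCR does not suit SAE patients who are still operated.
- *That power falls to 77.8%.* This needs every one of the 10% drop-outs to be a non-responder (27% v 36%, 395 per arm) and 30%/40% to be rates among the operated only. The sample size section says neither.

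**Conclusion.** The contradiction is real and touches the primary endpoint: the SAE sentence agrees with neither the end-of-trial list nor the intention-to-treat rule. Followed literally, it can make pCR missing almost only in the exercise arm, and no planned analysis departs from MAR.

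The size cannot be fixed from the Protocol. It is zero if these patients respond like the rest of their arm and under about one point at 1–2% exits. It becomes material only if exits reach about 5% or more and those patients rarely reach pCR. These ranges assume no exits in control, no pCR retrieved after exit, and imputation from arm and subtype only. The case for acting rests less on a large expected bias than on a one-sided, irrecoverable loss that a sentence can prevent.

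**What to change.** Reconcile the Ethical considerations, End of trial, Statistical analysis plan and Withdrawal sections. State that after an SAE, or after early end of NACT, pCR (including slides for central review) and follow-up are still collected and analysed as randomised unless the participant withdraws consent. Say explicitly whether discontinuing refers to the exercise or to the trial. Whether exercise itself stops is a clinical matter for the investigators, and no view is offered on it.

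With pCR collected from everyone operated, SAE exits no longer cause missing data. The sample size is unchanged.

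As a cheap addition to Handling missing values and deaths, add a sensitivity analysis that counts participants not operated because of progression or death as non-pCR. Keep it to that group. Scoring every SAE exit as a failure would err the other way: at 5% exits with q = 40% the difference would read 40% − 0.05 × 40% − 30% = 8.0 points instead of 10.

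The cost is wording, plus retrieval of routine pathology for a few patients. The downside of the added analysis is that the pCR rates and the difference may look slightly smaller.

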# Withdrawal

Patients who wish to withdraw from the trial may do so at any time, without providing a reason. Data already included in previous eCRFs will be included in the analysis if the participant does not explicitly wish to have his/her data excluded from analysis. Ceasing participation will be recorded in the eCRF.

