## Study calendar

| ***Time point*** |  | |
| --- | --- | --- |
| Baseline (before initiation of NACT) | - Verify eligibility - Informed consent - Three 14G tumour biopsies in addition to diagnostic biopsy* - Blood and plasma samples (4-5 x 10 ml) * - Faeces samples * - Full tumour biology (ER, PR, HER2, tumour grade, and Ki67)   Baseline questionnaires and testing   1. EORTC QLQ-C30 (quality of life) 2. EORTC QLQ-B23 (quality of life, breast cancer) 3. Sense of coherence (SOC-13) 4. Godin Leisure Time Self-Reported Physical Activity questionnaire 5. Self-Efficacy of Exercise (SEE) questionnaire 6. Hand grip muscle strength test 7. 1-RM leg press test 8. Ekblom-Bak submaximal cardiorespiratory cycle test 9. Amsterdam Cognition Scan 10. BMI, body fat composition, haemoglobin levels, blood pressure, demographics and medical history | |
| **Randomization** | ***Standard*: Usual care**  ***Intervention*: Physical exercise intervention** | |
| Pre-surgery | Repeat baseline questionnaires and testing (1.-2., 4.-8., 10.)  Device-measured physical activity (Fitbit activity tracker)  Blood (4-5 x 10 ml) and faeces samples *.  Record toxicity-related outcomes and treatment details (CRF) | |
| Surgery | Breast and axillary surgery: endpoint pCR assessed and recorded.  Tumour tissue collected and stored at trial biobank* | |
| Postoperative treatment | Adjuvant treatment as per clinical routine | |
| **Follow-up (years after surgery)** | **1** | **2** |
| EORTC QLQ-C30* | x | x |
| EORTC QLQ-B23* | x | x |
| Record recurrence and survival | x | x |
| Godin (physical activity)* | x | x |
| SEE scale | x |  |
| Amsterdam Cognition Scan | x |  |
| Faeces sample * | x |  |
| Device-measured physical activity (Fitbit activity tracker) | x |  |
| Self-reported sick leave | x | x |

* Stockholm sites only

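### A participant who leaves the trial during chemotherapy has no pCR in the primary analysis, because the Withdrawal section makes no provision for taking it from routine pathology

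*Protocol*

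**What the plan says.** The Statistical analysis plan section makes intention-to-treat the primary approach: "all study subjects will belong to the treatment group (exercise intervention or control) they were assigned to, disregarding compliance".

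The Withdrawal section lets participants leave the trial at any time. On data it states: "Data already included in previous eCRFs will be included in the analysis if the participant does not explicitly wish to have his/her data excluded". It names no lesser step, such as stopping the app or the tests while follow-up continues. The End of trial section adds that the trial also ends for "participants who die, withdraw consent or are lost to follow-up".

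pCR comes late. The Study calendar places it at surgery: "Breast and axillary surgery: endpoint pCR assessed and recorded". Outcomes, Variables and measures puts this about five months after chemotherapy starts, as standard of care, and plans central slide review for all cases.

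The sample-size section expects losses: "Accounting for a drop-out of 10%, we aim to include 790 patients".

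Four other places bear on the point:
- Population allows participants whose chemotherapy is stopped early to remain on the trial.
- Handling missing values and deaths plans multiple imputation under missing at random (MAR) for outcomes without repeated measurements, which include pCR, as a sensitivity analysis.
- Ethical considerations says that participants with a serious adverse event discontinue trial participation.
- Adverse Events asks for an event to be reported as serious only if it is at least possibly related to the trial intervention.

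**The concern.** The trial asks what assignment to exercise does to pCR. An intention-to-treat answer needs the pCR of everyone randomised. The protocol has no route to that result for a person who leaves between randomisation and surgery, even though the hospital will normally hold it. The primary comparison then rests on those who remained in the trial. If leaving is related to tolerance of treatment or to response, and differs between arms, the comparison is no longer protected by randomisation.

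The statement on serious adverse events adds a second source of loss. It ends trial participation, not just the intervention. Since reporting as serious depends on a relation to the intervention, exits imposed by the protocol may fall mainly on the exercise arm. That does not sit with an analysis that disregards compliance.

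**Working it through.** **1. The plan's own sample size.** Inputs from Estimated sample size and power: for controls, "It is anticipated that the rate of the primary endpoint pCR will be approximately 30% in the control arm"; the target for the exercise arm is 40%; and the size is given as "With a power of 80% and an alpha of 5%, a total of 712 patients have to be included; 356 in each arm". The Primary endpoint section gives a two-sided test. With pooled variance and mean rate 0.35:

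n per arm = [1.960 × √(2 × 0.35 × 0.65) + 0.842 × √(0.30 × 0.70 + 0.40 × 0.60)]² / 0.10² = 355.9, so 356 per arm and 712 in total.

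This matches. 712 / 0.9 = 791.1, close to the stated 790. The sample size is not in dispute.

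**2. How many lack pCR.** 0.10 × 790 = 79, about 39 per arm. The inflation from 712 to 790 makes sense only if drop-outs are expected to yield no pCR.

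**3. Which analysis they are missing from.** The primary logistic model needs an observed pCR. Imputation enters only as a sensitivity analysis, so the primary result rests on observed values.

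**4. Possible bias.** The protocol gives neither withdrawal by arm nor pCR among those who leave, so both are assumed here. Let p be an arm's pCR rate over all randomised, w the share that leaves and q the pCR rate of those who leave. The rate among those who stay is

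(p − w × q) / (1 − w).

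Take no true effect (p = 30% in both arms), 395 per arm, and a normal approximation for the type I error (nominal 5%).

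| Leave: exercise / control | pCR in those who leave | Exercise stayers | Control stayers | Spurious difference (points) | Type I error |
|---|---|---|---|---|---|
| 10% / 10% | 10% in both | 32.2% | 32.2% | 0 | 5.0% |
| 15% / 5% | 30% | 30.0% | 30.0% | 0 | 5.0% |
| 15% / 5% | 20% | 31.8% | 30.5% | +1.2 | 6.5% |
| 15% / 5% | 10% | 33.5% | 31.1% | +2.5 | 10.9% |
| 5% / 15% | 20% | 30.5% | 31.8% | −1.2 | 6.5% |
| 5% / 15% | 10% | 31.1% | 33.5% | −2.5 | 10.9% |

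Example, fourth row: (0.30 − 0.15 × 0.10) / 0.85 = 0.3353 and (0.30 − 0.05 × 0.10) / 0.95 = 0.3105, a difference of 0.0248.

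**5. Outer bounds.** Suppose stayers show 40% against 30% with 356 per arm (142.4 and 106.8 responders) and 39 per arm are missing.
- Worst case for exercise: 142.4/395 − (106.8 + 39)/395 = −0.9 points.
- Best case: (142.4 + 39)/395 − 106.8/395 = +18.9 points.

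These are limits, not expectations.

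**6. Power.** Recovering all 790 results would raise power from 80.0% to 83.9% if the difference stayed at 40% against 30%. If exercise drop-outs have the control rate, the as-assigned exercise rate is 0.9 × 40% + 0.1 × 30% = 39%. Power for 39% against 30% with 395 per arm is 75.9%.

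**The case against.** The Withdrawal section is a rule for retaining data. It does not say that nothing more may be collected, and the consent wording is not available to this review. That stands: the loss of pCR is inferred from that section together with End of trial and the drop-out allowance. Still, nothing in the protocol tells a site to record pCR after withdrawal, so sites may differ.

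A reader might infer that anyone who gives up the exercise programme loses their pCR. The protocol does not support this. Intention-to-treat disregards compliance. The per-protocol analysis removes participants below 65% of the programme, which presupposes that such people stay in the trial. Those who stop chemotherapy early may also remain. The point covers only people who leave the trial.

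A reader might also infer that the bias must favour exercise. The greater burden in that arm makes this plausible, but the protocol gives no withdrawal figures by arm, expects drop-out to be low in both arms, and the reverse pattern reverses the sign. Nor is a power gain established: step 6 shows that it depends on the pCR of those who leave, and the inflation to 790 already protects the planned power.

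The planned imputation brings all randomised participants back, but only in a sensitivity analysis. Under MAR it would largely give those who left the rates of similar participants who stayed, so it would not correct loss that depends on the unseen response.

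Finally, the definition of a serious adverse event in Adverse Events is wider than the reporting rule, so a concentration of exits in the exercise arm is possible, not certain.

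**Conclusion.** The point holds in a limited form. As written, leaving the trial before surgery means no pCR in the primary analysis, which falls short of the stated intention-to-treat aim and is mostly avoidable. About 79 of 790 participants are affected if the planned 10% drop-out occurs and consists of exits before surgery.

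The bias is zero if leaving is unrelated to response. With no true effect, it is also zero if both arms lose equal shares with equal pCR. It is 1.2 to 2.5 points in either direction, with a type I error of 6.5 to 10.9%, under an assumed 15% against 5% split and 10 to 20% pCR among those who leave. These rates are assumptions, not figures from the plan. The statement on serious adverse events under Ethical considerations and the intention-to-treat statement need to be reconciled. This is a worthwhile, cheap improvement. It does not show that the design is unsound.

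**What to change.** In the Withdrawal section, separate two levels:

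- **(a) Stopping trial activities** (exercise programme, app, tests or questionnaires). The participant stays in the trial and in the primary intention-to-treat analysis. pCR, RCB and survival are still taken from routine pathology, the medical file and registers.
- **(b) Withdrawing consent to further data collection.** Only data already recorded are used, subject to the participant's existing right to have them excluded.

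Record the level and its date in the eCRF, and align the End of trial section and the consent wording. Reconcile the serious adverse event statement under Ethical considerations with the intention-to-treat statement, so that leaving the intervention is distinguished from ending endpoint collection. This concerns data collection only, not when exercise should stop.

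The cost is a short protocol and consent amendment, an ethics submission and a small eCRF change. No visit or procedure is added: surgery and pathology are standard of care, and central slide review is already planned. Participants who choose level (b) will still lack pCR, so the planned imputation remains useful.
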